### Study outcomes

This study will evaluate both feasibility and exploratory clinical outcomes to determine whether a wearable biosensor (PneumoWave DC) system is suitable for use in supported accommodation settings with people who use opioids (Fig 4).

**Fig 4 pone.0326482.g004:**
[figure not shown]
Study Logic Model. Assumptions are: – the study will last 8 months, recruitment will be conducted opportunistically by hostel staff, the sensor will be worn by participants for at least 4 weeks continuously, ideally at all hours, every day.

Primary Outcomes

Feasibility of protocol delivery, including:Recruitment and retention ratesTimeliness and completeness of data collectionEstimated time participants wore the biosensorAcceptability and usability of the device, based on:Completion of self-reported drug use diariesResponses to participant satisfaction surveysQualitative feedback from participants and staffTechnical feasibility of sensor deployment, including:Total hours of usable chest motion data collectedProportion of successful data recordingsOperational issues (e.g., battery replacement, electrode adhesion, connectivity)

Secondary outcomes

Event detection capability, including:Number of events where reduced or absent chest movement was detectedConcordance between staff/participant-reported overdose events and sensor dataSignal quality assessment at the time of suspected overdose eventsExploratory evaluation of algorithm relevance, including:Qualitative comparison of traces from suspected overdose and non-overdose periodsClassification of event detection outcomes (true positive, false positive, false negative)

#### Quantitative measures.

Approximately four weeks after enrolment, a subset of participants and hostel staff are invited to take part in semi-structured interviews. These explore perceptions of the biosensor’s usability, comfort, acceptability, and perceived value. A topic guide will be used and adapted iteratively. Interviews are audio recorded, transcribed, and anonymised for analysis. Where feasible, focus groups are also conducted with staff to explore operational perspectives and overdose response integration.

#### Qualitative interviews.

To explore participant experiences and perceptions of the PneumoWave DC system, semi-structured qualitative interviews will be conducted approximately four weeks after the initiation of data collection. These interviews will provide insights into usability, acceptability, and any challenges encountered while using the biosensor. A structured topic guide will be used to ensure consistency across interviews while allowing for open-ended responses (Supplementary File). This guide will include questions on ease of use, perceived benefits, privacy concerns, and the impact of the biosensor on participants’ daily lives.

Interviews will be conducted face-to-face in a private setting within the supported accommodation facility to ensure confidentiality and participant comfort. Interviews will be audio-recorded with consent from the participant and transcribed verbatim for thematic analysis. Focus groups or interviews with accommodation staff will also be conducted to gather perspectives on the feasibility of implementing the biosensor within supported housing environments. These discussions will explore staff experiences with participant recruitment, device adherence, and any operational challenges that arose during the study.

#### Rationale for study procedures.

Several key decisions were made in designing this study to maximise feasibility and data quality:

Drug diaries: Self-reported drug use diaries were chosen as they allow for frequent participant input, utilised for matching self-reported substance use recorded chest motion data. This method was also successfully utilised in RESCU-1, making it a logical approach for RESCU-2 to maintain consistency.Study setting selection: Supported accommodation settings were chosen due to their role in supporting individuals who might be at risk of overdose. This setting allows for real-world assessment and evaluation of biosensor use, which is essential for its future potential in these settings to prevent fatalities.Use of a Hub for data transmission: Instead of relying on participants’ personal devices or providing a smartphone or tablet, the study employs a dedicated Hub to collect and transmit biosensor data. This decision was made in collaboration with accommodation staff for a number of reasons: to reduce technological barriers, ensure reliable data capture across different sites, reduce vulnerability to theft, or risk that the devices could be sold.Participant and Patient Involvement (PPI) and a senior qualitative researcher (PR) informed the topic guide of the study

### Data collection and management

All collected data in the study will be pseudonymised. CRF data will be securely stored on a University of Dundee server. Data entry will be conducted in an encrypted Excel spreadsheet, with de-identified participant codes ensuring confidentiality. Qualitative interviews will be transcribed and anonymised before analysis.

Data from the biosensor will be uploaded securely and automatically to the Hub stored in a small container, located within the hostels. The data storage platform (supplied by Galen Data) complies with Health Insurance Portability and Accountability Act (HIPAA) requirements as set forth in the Galen Cloud HIPAA Compliance Matrix (004–0020), General Data Protection Regulation (GDPR) requirements as set forth in the Galen Cloud GDPR Compliance Matrix (004–0021), and California Consumer Privacy Act (CCPA) requirements. Additionally, Galen Cloud deployed on AWS is HITRUST certified.

A Trial Steering Committee and Data Monitoring Committee will be convened independently from the Sponsor for this study and will meet regularly to monitor the progress of the study and data collection and analysis.

### Ethical and safety considerations

The study is conducted in accordance with Good Clinical Practice (GCP) guidelines and has received ethical approval from the appropriate Research Ethics Committee (REC) from the University of Dundee (UOD-SMED-SLS-Staff-2024-24-107). The Sponsor for the study is University of Dundee.

Written and informed consent will be taken from all participants prior to any study procedures, including both sensor deployment and participation in interviews. Consent is taken by trained research staff or hostel staff and is treated as an ongoing process. Participants have the right to withdraw at any time without consequences. A sample consent form is included as a Supplementary File.

### No minors are involved in the study

Participants experiencing an overdose during the study will receive standard intervention from site staff. An Adverse Events form will be completed and as long as participants continue to fulfil the eligibility criteria they will remain in the study. The biosensor will remain in place during medical interventions when feasible. Ethical safeguards include ensuring that participants understand they can withdraw at any time without penalty.

For qualitative data collection, interviews and focus groups will be audio-recorded with explicit, written informed consent from all participants. Interview recordings will be transcribed verbatim for thematic analysis. Interviews with accommodation staff will also be conducted to gather implementation perspectives, with the same consent procedures applied.

### Statistical and qualitative analysis

The analysis plan is registered on Open Science Framework with the Study Logic model (reference: osf.io/m67nr). Both quantitative and qualitative data will be analysed to assess the feasibility, acceptability, and technical performance of the PneumoWave DC system in supported accommodation settings.

#### Quantitative analysis.

Descriptive statistics will be used to describe the number of events, evidence of reduced and no chest movement collected by the DC system, participant demographics, self-reported drug use, engagement with the device, and responses to satisfaction surveys.Key feasibility indicators, such as device wear time, frequency of use, and reported usability issues, will be examined.Measures of variability will be calculated to assess consistency of device use across different participants and sitesAnalyses will explore differences based on demographic factors, prior overdose history, and frequency of opioid useIf sufficient data are available, exploratory inferential statistics may be conducted to examine relationships between variables.

#### Qualitative analysis.

Thematic analysis will be conducted on interview and focus group transcripts to identify recurring themes related to feasibility, acceptability, and perceived benefits or barriers to using the biosensor.A coding framework will be developed iteratively, with transcripts independently reviewed by multiple researchers to ensure consistency.Attention will be given to both participant and staff perspectives, highlighting differences in experiences and expectations regarding the technology.Data saturation will be assessed to ensure that key themes are adequately represented across participant responses.

### Quantitative analysis

For the hostel outcome measures (e.g., demographic data) and satisfaction survey, descriptive statistics will be reported using means and standard deviation for continuous data. Absolute numbers and percentages will be reported for categorical data. Any statistical software can be used.

Key feasibility indicators include:

Number of participants enrolled and retainedTotal hours of usable biosensor data recordedPercentage of completed self-reported drug use entriesFrequency and nature of technical issues (e.g., battery replacement, electrode use)Timeliness and completeness of overdose reporting from staff

### Biosensor analyses

#### Reference event.

Evidence of reduced and no chest movement within the sensor data will be compared to the observed and recorded reference events. Reference events will comprise of staff observed events and reports and drug use diary records. Staff-identified events are any event that has required an intervention by staff in the hostel. Interventions can range from a simple audio stimulus, up to and including requesting an ambulance to attend. These events include those where overdose may not have occurred, but the response will have been managed in the same way according to the site’s incident response. These incidences will be recorded as an ‘acute event’ or ‘prompt event’. Where an overdose has been clearly identified using the tools mentioned above, these incidences will be identified as ‘overdose event.’ Analysis will incorporate both types of ‘reference’ events. Biosensor data will be analysed over a period of 30 minutes prior to each reference event. We expect the following possible scenarios to occur: 1) no opioid use reported, overdose event; 2) opioid use reported but no overdose event; 3) opioid use and overdose event.

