## Abstract

**Background:**

People who overdose on opioids when they are alone or unmonitored are at heightened risk of death as other people do not know they should provide an emergency response. Wearable technology provides an opportunity to continuously measure respiratory function and ultimately send an alert if respiratory depression occurs.

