Previous research has demonstrated that wearable biosensors have significant potential for improving health monitoring in various medical contexts, including respiratory diseases such as chronic obstructive pulmonary disease (COPD) and sleep apnoea. Other studies have investigated the use of technologies for opioid-induced respiratory depression, more specifically, studies testing various sensors and devices highlight the potential for wearable real-time monitoring for overdose prevention [12–14]. However, despite these advancements, the practical application of biosensors for harm reduction remains understudied. Most research to date has been conducted in controlled environments such as hospitals or supervised injection sites, leaving a gap in understanding how these devices perform in real-world, community-based settings. This study, RESCU-2, aims to bridge that gap by evaluating the feasibility and acceptability of PneumoWave Biosensor within homeless hostel or supported accommodation environments (equivalent to Housing First in the USA) where individuals may use opioids in private, unsupervised conditions. Supported accommodation facilities provide an opportunity to implement life saving interventions when notified in environments where individuals are already receiving services and support. This study builds upon findings from the RESCU-1 study which explored the feasibility of respiratory monitoring in people recruited in treatment clinics and needle exchanges, and who self-report their drug use.

This study aims to evaluate the feasibility, acceptability, and technical implementation of a wearable biosensor (PneumoWave DC system) to record chest motion in individuals at risk of opioid overdose living in supported accommodation.

The primary objectives are to:

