Assess the feasibility of implementing the study protocol within supported accommodation settings. This includes recruitment and retention of participants, adherence to study procedures, and overall completeness of data collection.Evaluate the acceptability and usability of the biosensor system among residents who use opioids. This will be informed by participant engagement, qualitative feedback, and satisfaction survey responses.Assess the acceptability of the biosensor system among hostel staff and key stakeholders, particularly those involved in overdose response.Determine the technical feasibility of capturing chest motion data using the PneumoWave DC system in this setting, and evaluate its potential to contribute to overdose detection algorithm development.

Secondary objectives include:

Descriptive analysis of events where sensor data corresponds to suspected opioid overdose episodes, based on staff reports or participant accounts.Evaluation of the system’s ability to detect changes in recorded chest motion during suspected events and to differentiate overdose-related respiratory suppression from typical patterns.Exploratory comparison of biosensor traces from overdose and non-overdose periods to assess system sensitivity and specificity in identifying overdose events.

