#### Algorithm under test.

The PneumoWave Hub transmits Biosensor data to a Cloud Storage facility. The stored data is then processed using experimental algorithms for the presence of reduced chest movement events.

The performance of the Algorithm (Under Test, AUT) will be compared to the reference events at the hostels in terms of the AUT’s sensitivity and false alarm rate, if this is possible. If the target numbers for sample size and acute events are not reached, analysis will still be possible and feasible, but it may be exploratory.

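### An overdose that nobody finds or reports cannot enter the reference set, so the exploratory false alarm rate is inflated outside reference events and sensitivity covers reported overdoses only

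*Protocol article*

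**What the plan says.** The Background of the abstract gives the motivation: "People who overdose on opioids when they are alone or unmonitored are at heightened risk of death". The Introduction describes the setting as one "where individuals may use opioids in private, unsupervised conditions".

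The reference standard is fixed under Reference event: "Reference events will comprise of staff observed events and reports and drug use diary records". The staff component is then defined: "Staff-identified events are any event that has required an intervention by staff in the hostel". The secondary objectives in the Introduction describe suspected overdose episodes as "based on staff reports or participant accounts", and Study procedures has hostel staff complete a form for overdoses that are seen or reported to them.

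Reference event also sets the time frame: "Biosensor data will be analysed over a period of 30 minutes prior to each reference event". It lists three expected scenarios, one of which is "2) opioid use reported but no overdose event". Algorithm under test says performance will be judged by "sensitivity and false alarm rate, if this is possible". The secondary outcomes under Study outcomes allow three classes for event detection: true positive, false positive and false negative. The article describes no unverified class.

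**The concern.** The reference is incomplete in the very place the device is meant to work. Someone who overdoses alone, recovers without staff noticing and tells nobody leaves no reference event. A correct detection of that episode then counts against the algorithm, and a missed one does not count at all.

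The drug diary does not close the gap. It records use, and use without a recognised overdose falls into the scenario of opioid use with no overdose event. If neither use nor overdose is recorded, the episode fits none of the three listed scenarios.

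At stake are the secondary objective on sensitivity and specificity and, less directly, the primary objective on the system's potential for algorithm development. An algorithm could look worse than it is because it finds what staff do not. It could also look better than it is if it misses episodes that nobody else saw. The limitations sections mention self-report and incomplete diaries, but do not draw this consequence.

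**Working it through.** The article states no accuracy figure, event rate or capture rate, so there is none to reproduce. The check has two parts.

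**1. Where an overdose that is neither found nor reported can go**

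- Detected: no overdose event exists to match it, so it cannot be a confirmed true positive. It is not a false negative, because it was detected. Only false positive remains. If it falls in a window tied to a diary record, the match is to drug use and not to an overdose.
- Missed: there is no reference event to miss, so it is never a false negative.
- Time frame: if only the 30 minutes before reference events are analysed, a detection elsewhere is not scored at all. But a false alarm rate and a comparison with non-overdose periods both need time outside those windows. The two sections do not fit together as they stand. On either reading the detection gets no credit.

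**2. Size, as an illustration**

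From the article: 2,000 planned participant-days (Setting and participants). Assumed: N = 10 true overdoses; sensitivity s = 0.90; share captured by the reference w = 0.75, 0.50 or 0.25; truly false alarms F = 0, 10 or 100, none coinciding with a reference event.

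- Scored true positives = N × w × s
- Correct detections scored as false = N × (1 − w) × s
- Scored false positives = F + N × (1 − w) × s
- Apparent positive predictive value (PPV) = scored true positives / (scored true positives + scored false positives)
- Excess per 1,000 participant-days = N × (1 − w) × s / 2,000 × 1,000

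| w | Scored true positive | Correct but scored false | Excess per 1,000 participant-days | Apparent PPV, F = 0 (true 1.00) | Apparent PPV, F = 10 (true 9/19 = 0.47) |
|---|---|---|---|---|---|
| 0.75 | 6.75 | 2.25 | 1.1 | 0.75 | 6.75/19 = 0.36 |
| 0.50 | 4.5 | 4.5 | 2.3 | 0.50 | 4.5/19 = 0.24 |
| 0.25 | 2.25 | 6.75 | 3.4 | 0.25 | 2.25/19 = 0.12 |

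The share of correct detections that is mislabelled is N(1 − w)s / (Ns) = 1 − w, whatever N and s are. The relative effect on the false alarm count depends on F. With F = 10 the scored count is 12.25, 14.5 or 16.75, about 23%, 45% or 68% too high. With F = 100 it is 102.25, 104.5 or 106.75, only about 2% to 7% too high.

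For sensitivity, write s_c for captured and s_u for uncaptured overdoses. The overall value is w × s_c + (1 − w) × s_u. With s_c = 0.90 and an assumed s_u = 0.60, the study would report 0.90, while the overall value is 0.825, 0.75 or 0.675 for w = 0.75, 0.50 or 0.25. If s_u = s_c, there is no difference. The article does not say which applies.

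**The case against.** The strongest reply has four parts.

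- **The label is inferred.** The article never defines a false positive or says how an unmatched detection is scored. Matching rules may stand in the registered analysis plan, which is not shown. That is fair, but the reference sources, the measures and the three classes are stated here, and they leave no class in which such a detection is correct.
- **The reference is wider than staff-witnessed events.** A reader might infer that every unwitnessed overdose is lost. The documents do not support this: participant accounts count, and an overdose that staff discover later and respond to can enter. The gap is limited to episodes neither found nor reported.
- **The net direction of bias is not established.** A reader might infer that the whole false alarm rate is biased upward. But the reference also takes in acute or prompt events that may not have been overdoses, as well as diary records. A spurious detection that coincides with one of these would be matched, which lowers the apparent rate. Upward bias can be claimed only outside reference events. Nor can one say that staff events are those with the clearest signs, since an intervention as slight as a sound prompt qualifies.
- **The outcomes are exploratory.** The article hedges the accuracy measures as conditional on being possible and makes no claim of accuracy for overdose in private rooms. This stands, and it limits the weight of the point.

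**Conclusion.** The point holds in a limited form. Overdoses that are neither found by staff nor reported cannot be confirmed by this reference. Detecting one adds to false alarms outside reference events, and missing one leaves no trace. The reported sensitivity therefore applies to captured overdoses and cannot be carried over to overdose when alone.

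The size is unknown. The mislabelled share of correct detections equals the uncaptured share of overdoses, so 25% to 75% over the assumed range. The effect on the false alarm count runs from about 2% (F = 100, w = 0.75) to about 68% (F = 10, w = 0.25), all under assumed values. If there were no truly false alarms, every scored false alarm would be a mislabelled correct detection.

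The primary feasibility and acceptability outcomes are not affected. A reader might infer that the study's main results are undermined, but accuracy is a secondary, exploratory outcome. This is an inexpensive improvement that changes what that outcome can conclude.

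**What to change.** In the secondary outcomes under Study outcomes, and in Reference event and Algorithm under test:

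- (a) For unmatched detections, replace the false-positive class with one named detection without a matched report. Give its rate per 24 usable hours, and state that it is an upper bound on false alarms outside reference events only.
- (b) Report detections matched to overdose events separately from those matched to acute or prompt events, and from those matched to diary-only records. Without this split, spurious detections that match non-overdose events would be hidden.
- (c) Label sensitivity as applying to staff- or participant-reported overdose events.
- (d) Reconcile the 30-minute window with the false alarm rate by stating which recording time outside the windows is scored.
- (e) Use the trace comparison already planned to describe unmatched detections, split by whether a diary entry of opioid use precedes them.

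No new data are needed. The cost is some wording, one extra descriptive table and a more modest accuracy claim. Status and timeline says that no results had been generated at the time of writing, so on the article's account the change could precede the analysis.

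### The reference events for algorithm sensitivity include staff interventions without overdose, so the figure as written is not the sensitivity to overdose named in the objective

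*Protocol article*

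**What the plan says.** **Target.** In the protocol article, the last secondary objective in the Introduction is an exploratory comparison of sensor traces "to assess system sensitivity and specificity in identifying overdose events". Under Study outcomes, the secondary concordance outcome is likewise confined to overdoses reported by staff or participants. A further outcome classifies detections as true positive, false positive or false negative.

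**Reference standard.** Under Biosensor analyses, the Reference event section is wider: "Reference events will comprise of staff observed events and reports and drug use diary records". It continues: "Staff-identified events are any event that has required an intervention by staff in the hostel". The threshold is low: "Interventions can range from a simple audio stimulus, up to and including requesting an ambulance to attend". Non-overdose events are in the set by design: "These events include those where overdose may not have occurred, but the response will have been managed in the same way". These are labelled acute or prompt events. Overdoses get their own label: "Where an overdose has been clearly identified using the tools mentioned above, these incidences will be identified as" overdose events. The section then says that both types enter the analysis, with sensor data examined over the 30 minutes before each reference event.

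**Performance measure.** The Algorithm under test section says: "The performance of the Algorithm (Under Test, AUT) will be compared to the reference events at the hostels". The measures are sensitivity and false alarm rate, if this proves possible. Nothing limits the sensitivity denominator to overdose events.

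**The concern.** Sensitivity is the share of true cases that are detected, so it depends on what counts as a case. The objective makes the case an overdose. The analysis section makes it anything that prompted staff to act, down to speaking to a resident.

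Two errors of classification follow. If staff rouse someone who has not overdosed and the algorithm stays silent, the event is scored as a miss. If the algorithm alerts, the event is scored as a true positive, although against the overdose objective it is a false alarm. Both the sensitivity and the false alarm rate are affected, and the true positive, false positive and false negative classification inherits the problem.

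The Introduction also makes the system's potential contribution to overdose detection algorithm development part of a primary objective. A percentage labelled sensitivity that mostly reflects how often staff prompted residents would misinform that work.

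**Working it through.** The article states no sensitivity, event count or expected share of overdoses, so there is no figure to reproduce. The check sets the two definitions side by side and then illustrates the effect of pooling.

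**Step 1. How a staff event is scored**

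| Staff event | Algorithm | Against the overdose objective | Against the reference events as written |
|---|---|---|---|
| Overdose | alerts | true positive | true positive |
| Overdose | silent | false negative | false negative |
| Prompt, no overdose | alerts | false positive | true positive |
| Prompt, no overdose | silent | true negative | false negative |

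The two standards disagree on every non-overdose event.

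**Step 2. Formula**

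Pooled figure = π × Se + (1 − π) × q, where
- π is the share of reference events that are overdoses,
- Se is the true sensitivity to overdose,
- q is the chance that the algorithm flags the 30 minutes before a non-overdose event.

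All three are assumptions, because the article gives none of them.

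**Step 3. Results with π = 20%, staff events only**

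| Se | q = 0 | q = 5% | q = 10% | q = 20% | q = 30% |
|---|---|---|---|---|---|
| 80% | 16% | 20% | 24% | 32% | 40% |
| 90% | 18% | 22% | 26% | 34% | 42% |
| 100% | 20% | 24% | 28% | 36% | 44% |

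Example in counts: 10 overdoses and 40 prompts, Se = 90%, q = 10%, give (10 × 0.9 + 40 × 0.1)/50 = 13/50 = 26%.

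**Step 4. What drives the figure**
- Raising Se from 80% to 90% moves it by 0.2 × 10 = 2 percentage points.
- Raising q from 0 to 30% moves it by 0.8 × 30 = 24 points.
- At Se = 90% and q = 5%, changing π from 20% to 50% moves it from 22% to 47.5%. Lowering π to 10% gives 13.5%.

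An algorithm that is perfect for overdose (Se = 100%, q = 0) scores 20%. One that also alerts at 30% of non-overdose events scores 44%, so the pooled figure rewards the less specific algorithm.

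**Step 5. After restriction to overdose events**

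With π = 1 the formula returns Se whatever q is, which is the quantity in the objective.

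**The case against.** **Pooling is not stated outright.** The events carry separate labels, and incorporating both types could mean stratified reporting. A registered analysis plan, not shown here, may do that. This is a fair point and it lowers the severity: overdose-only sensitivity can be computed from the labelled data. But the article names the reference events as the comparator, without restriction, and does not use the labels there. That is a stated rule at odds with the objective. If the registered plan does separate the types, the article's wording still has to be aligned with it.

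**The algorithm looks for reduced chest movement.** A resident whom staff roused may truly have had reduced movement, so an alert there need not be wrong. That supports reporting how often the algorithm flags prompt events. It does not make the result sensitivity to overdose.

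**Stronger readings that a reader might infer.** The text does not support three of these.
- *Every diary entry is a positive.* The defining sentence does list diary records. With 5 overdoses, 20 prompts and 500 diary entries, at Se = 80% and q = 5%, the figure would be (4 + 1 + 25)/525 = 5.7%. But the reference to both types most naturally means acute or prompt events and overdose events. The section treats reported use without overdose as a scenario of its own, and the rationale for study procedures describes the diary as a means of matching reported use to chest motion. The 5.7% is therefore not relied on.
- *An episode recorded by both staff and diary is counted twice.* No section says so, and the scenario of opioid use with overdose suggests a single episode.
- *The plan claims that sensitivity can be estimated however few events occur.* The sentence "If the target numbers for sample size and acute events are not reached, analysis will still be possible and feasible" goes on to say that the analysis may then be exploratory, and the sentence before it makes the comparison conditional on being possible.

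**Conclusion.** The reference standard in the Biosensor analyses does not match the secondary objective or the concordance outcome. Followed as written, the reported figure is not sensitivity to overdose, and the false alarm rate is affected too. With true sensitivity 80–90%, overdoses 20% of staff events and an alert rate of 0–30% on the rest, the pooled figure is about 16–42%. Every input to that range is assumed. The direction and the dependence on event mix follow from the definition whenever non-overdose events are numerous and are flagged less often than overdoses.

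Severity is moderate. The analysis is secondary, exploratory and conditional, no data are lost, and the primary feasibility outcomes on recruitment, wear time, usable data and acceptability do not depend on it. A reader might take this as a flaw that undermines the study, which the documents do not support.

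**What to change.** Change the wording of the Reference event and Algorithm under test sections as follows:
- Define the positives for sensitivity as overdose-event episodes only.
- Report acute or prompt events without overdose as a separate stratum, as a detection frequency and not as sensitivity.
- State that diary-reported use without overdose is non-overdose comparison time for the false alarm analysis.
- State that diary and staff records of one episode are one event.
- Call algorithm performance exploratory whatever the number of events, in line with the Introduction.

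Interval methods and any minimum event count can be left to the analysis plan.

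The labels already exist, so no data collection changes. The cost is fewer events and a wider interval. As an illustration, 2,000 participant-days is 2,000/365.25 = 5.5 person-years. At an assumed 0.2 to 2 overdoses per person-year, 1.1 to 11 would be expected. Exact 95% intervals would be 28.4–99.5% for 4 of 5 detected and 48.2–97.7% for 9 of 11. That imprecision is real whichever denominator is printed, and it is why the exploratory label should not depend on the event count.
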